**Intervention Arm**

For those assigned to the intervention arm, rather than offering access to the full ARMADILLO architecture at once (the extensiveness of which would make immediate assessment of relevant outcomes difficult), they will instead be provided access to one new domain (SRH topic) every week (Day 1 of 7 of a given week) and assessed on domain-specific outcomes at the end (Day 7 of 7) of that week. Within this domain, they will have the ability to navigate freely across and between messages, accessing subdomains that interest them and ignoring those that don’t. At the start of the next week (Day 1 of 7), access to the previous week’s domain is closed – meaning that the user can no longer access the information in that domain, though any messages the user has already received remains in his/her phone unless deleted by the user. At the same time, the next domain is ‘unlocked’ and the user receives a message alerting them to this new access.

Progression through the intervention will be as follows:

- Start of Week 1: an SMS alerting intervention participants to a new domain is pushed to their phones (e.g. ‘You’ve unlocked PREGNANCY. Want to learn more? Send ‘ARMADILLO’ to XXX – free and confidential! Stay tuned for a quiz at the end of the week to win free airtime!’).
- Week 1, Days 1-7: participants can access all subdomain messages in either Swahili or English (Kenya) or Spanish (Peru) within this given domain, as many times as they would like, without charge.
- Week 1 (Day 7): a set of 3-5 close-ended SRH outcome-assessing questions are pushed via SMS to the participants’ phones. Participants receive free airtime for any response (whether or not it is correct).
- Week 2, Day 1: access to Week 1 domain ends and intervention participants receive an SMS alerting them to the new domain they can now access.
- Weeks 2-7: The pattern described for Weeks 1 and 2 continues until participants have received one week of access to all domains. Access is not cumulative.

**Control Arm**

Some participants will be randomly allocated to the control arm. Control arm participants will receive no messages on their phone during the intervention period. Instead, they will only participate in baseline (described above), and end-intervention and follow-up assessments (described below).

**Arm 3: ‘Contact’(Kenya), ‘Push’ (Peru)**

The third arm has been developed in close collaboration with each study site, and aims to address specific questions from countries and/or the digital health literature.

Kenya

In Kenya, the third arm will serve as a ‘contact’ arm, assessing whether changes in outcomes are attributable to the content of the intervention or rather the participant-contact nature of the intervention itself. As such, the inclusion of a ‘contact’ arm will match system-initiated contact with study participants without providing them access to ARMADILLO content. If the success of this digital health intervention is merely in participant contact (i.e. encouraging users to consider a relevant SRH topic) rather than the content of the ARMADILLO platform, we will find no differences in outcomes between intervention and contact arms and participants in both arms would likely have better outcomes than control participants.

Participants in Kenya’s contact arm will not have access to ARMADILLO message content. They will, however, receive the same number of system-initiated contacts (pushed messages) that intervention arm receives: specifically, they will receive messages alerting them to a new SRH domain at the beginning of each week, and the domain-specific assessment at the end of the week. Contact participants will receive each domain as a ‘topic of the week’ and their weekly introduction SMS will encourage them to learn on their own that week; no additional information on that topic will be provided.

Progression through the contact arm will be as follows:

- Start of Week 1: an SMS alerting contact participants to a ‘topic of the week’ is pushed to their phone (e.g. ‘This week’s topic is PREGNANCY. Find out what you can about pregnancy, test your knowledge with our quiz at the end of the week and win free airtime!’).
- Week 1, Day 7: There is no further interaction with the contact arm until the end of the week, when a set of 3-5 close-ended SRH outcome-assessing questions about that week’s topic are pushed via SMS to the participants’ phones. Participants receive free airtime for any response (whether or not it is correct).
- Week 2, Day 1: access to Week 1 topic ends and contact participants receive an SMS alerting them to the new topic that they can now learn about.
- Weeks 2-7: The pattern described for Weeks 1 and 2 continues until participants have received one week of suggested topics.

Figure 3 shows the progression of all three arms in Kenya.

**Figure 3**

[figure not shown]

Peru

In Peru, push-message public health campaigns are the norm for a wide variety of sensitive (re: HPV vaccination) and non-sensitive (maternal health, nutrition, etc) health campaigns. Bi-directional interventions, such as ARMADILLO, do not exist; this will make the format of the ARMADILLO intervention arm a novelty for Peru. As such, Arm 3 for Peru will adopt the Peruvian ‘push system’ norm, answering a question important for adoption and scale up to national level in this context: is free, active engagement – while a novelty in this setting – better for engaging with young users than passive receipt and reading of messages (the norm in Peru)?

Progression through the push arm will emulate existing public health campaigns in Peru and will be as follows:

- Start of Week 1: an SMS alerting participants to a ‘topic of the week’ is pushed to their phone (e.g. ‘This week’s topic is PREGNANCY. Not interested? Respond XX to opt out this week’).
- Week 1, Day 2-5: 1-2 SMS messages are at the same time daily (evening, when participants have left school, where phones are not generally allowed) to participants’ phones, covering various subdomains from the week’s topic
- Week 1, Day 6: At the end of the 1-2 SMS messages which are pushed to phones, participants have an option to ‘responde XX para leer mas’ [respond to read more]. If they respond, they will immediately receive an additional maximum of 4 messages.
- Week 1, Day 7: Close-ended SRH outcome-assessing questions about that week’s topic are pushed via SMS to the participants’ phones. Participants receive free airtime for any response (whether or not it is correct).
- Week 2, Day 1: access to Week 1 topic ends and push participants receive an SMS alerting them to the new topic that they will now learn about.
- Weeks 2-7: The pattern described for Weeks 1 and 2 continues until participants have received one week of suggested topics.

Figure 4 shows the progression of all three arms in Peru.

**Figure 4**

**
[figure not shown]
**

Arm 3 and intervention participants in both sites will progress through domains sequentially, based on numbers assigned to each domain (for example, a participant starting at Domain 1 would progress through Domains 2-7 in order in the following weeks). However, participants will be randomized as to which number domain they start with, in order to account for participant recall bias at the end-intervention assessment as a result of having seen one domain 7-8 weeks ago and another one week ago. For example, an intervention/Arm 3 participant may be randomly assigned to start at Domain 3, meaning they would cycle through Domains 4-7 in the following weeks before finishing with Domain 1 and 2. It should be noted that the free airtime intervention and Arm 3 participants receive – meant to subsidize perceived expense for participating in the system – will be credited to users by the study team and does not require negotiation with the mobile network operating companies (MNOs).

End-intervention assessment

Participants from all three arms will be asked to return for an in-person assessment of all outcomes at the end of the intervention. Participants will be able to fill out the end-line survey individually in a private space. Research team members will update participant contact information if necessary and alert participants that they will be invited back for a follow-up assessment in two months

At this visit, a selected sub-sample of intervention participants will also be invited to participate in an in-depth interview. A trained member of the research team will consent these participants and conduct the interview. This interview will provide an opportunity for participants to provide feedback on their experience and opinions using the system. Of particular interest will be recommendations for system improvement; if and with whom they shared messages; perceived ease or difficulty in translating knowledge obtained through ARMADILLO into action (if action was desired or necessary); where they obtained contraception (if applicable); and any recommendations for improving the experience of obtaining contraception.

In Peru, this sub-sample of participants to be interviewed will be evenly split between intervention and Arm 3 (push arm) participants (10 participants interviewed from each arm). This will allow a comparison of user experiences between the push arm (the current standard in Peru) and intervention arm (a novelty), the data from which will be important an important complement to survey data in deciding on a format for scale-up in future planned phases.

Follow-up assessment

There will be no contact with participants from any study arm in the eight weeks between the end of the intervention and follow-up. The ARMADILLO system will be offline in this period as well. Two months following the end-line assessment, intervention, control, and Arm 3 participants will be brought back for an in-person, follow-up assessment of all SRH outcomes.

Starting at Week 7 after the completion of ARMADILLO, the research team will contact participants again, to schedule a time - at the participant’s convenience – when the participant can return to the study site to complete one final, in-person assessment around the SRH outcomes. Raffles and airtime may also be used to encourage participants to return for the follow-up assessment.

Following the completion of the in-person assessment, returning participants in all arms will be provided with a short code to access the full ARMADILLO system. In the event that the system must undergo substantial revision prior to finalization, study participants will be told that they will be alerted via SMS when the final system is ready for access.

Participants will be able to fill out the baseline survey individually in a private space.

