***Participants***

For the purposes of this trial, where increased interaction with the system is anticipated and use of the phone for outcome measurement and follow-up is necessary, phone ownership is a requirement for participation. The same selection criteria will apply also to youth recruited for participation in the FGDs prior to the start of the effect assessment.

Eligibility criteria for the general ARMADILLO study is as follows:

- Youth between the ages of 13-24 (age range narrowed as needed for each site);
- Literate
- Have their own mobile phone (meaning it is primarily in their possession, and they control when and with whom they share access) and report regular use
- Have a mobile phone with them at the time of recruitment
- Report current use of text messaging

Recruitment to the FGDs preceding the trial will be purposive. Recruitment to the trial itself will be rolling over a one month period (recruitment is described more fully in the following section). Participants will be consented at their homes. Depending on the comfort level of the participant, they will continue either in their homes or be invited to meet a central location to participate in the baseline survey and be enrolled in one of the three ARMADILLO study arms. Randomization into intervention, control or Arm 3 arms will take place following completion of the baseline survey, with their seven-week interaction with the appropriate system commencing the following day. A research team member who is NOT interacting with participants will oversee the randomization of incoming phone numbers to the three arms.

In-depth interview (IDI) participants will be randomly sampled from within the pool of participants who, during their consent process, indicated they would be willing to participate in an IDI. Ten youth females and ten youth males from each country site will be selected by computer. At their end-line in-person assessment, members of the research team will invite the selected participants to participate in the IDI. Should any members indicate that they are no longer willing to participate, the computer will randomly select additional participants from the remaining pool.

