***Timeline:***

ARMADILLO Stage 2 is estimated to take approximately 12 months. The initial three months will involve preparatory activities, including:

- obtaining ERC approval and local IRB approval;
- recruiting and training data collectors;
- developing the technology architecture of the Stage 2 intervention/contact/control (inputting message content, developing message flows, obtaining short codes from mobile network operators

FGDs prior to the start of the intervention are expected to take a maximum of two months, which includes:

- recruitment, scheduling, and conducting the FGDs
- rapid analysis of results to incorporate any unexpected findings into messages/study instrument as necessary

The intervention itself is anticipated to last an additional five months, which includes:

- ~1 month for full recruitment
- Two months for the intervention itself
- An additional two months until the last-enrolled participant completes their two-month follow-up visit

Finally, an additional two months will be spent on reporting and dissemination of the

Stage 2 research results.

Please see Form IV for the detailed Gantt chart.

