***Incentives***

For all in-person interactions (initial recruitment, completion of end-line survey, and follow-up activities), participants will be reimbursed for travel costs as is appropriate at the time research activities are conducted. For in-person data collection, participants may also be provided with beverage and/or food during the data collection.

Participants will be reminded at many points throughout the intervention that their participation will not incur any SMS charges. Additionally, in order to combat traditional loss-to-follow-up and engagement-drop-off that digital health interventions face, as well as to reinforce the concept that study participation is free, all participants in the intervention arm and Arm 3 in both sites will be given token amounts of phone credit for responding to the study’s quiz questions delivered via SMS. Any response (not just correct responses) will receive phone credit.

Small phone credit disbursements such as those proposed above are typical in this research context and appropriate in these settings considering what is being asked of the participants. Travel reimbursement mentioned above is intended to make study participation affordable, but not coercive, to all eligible participants.

Benefits to participation in this study are the opportunity to learn about youth sexual and reproductive health. Intervention participants will have access to ARMADILLO message content while control participants will be encouraged to explore and research SRH domains they may not have traditionally had information on. At the end of the full intervention and follow-up period, the full ARMADILLO system will be made available to all study participants (intervention, contact, and control).

With regards to the study methods themselves, all information collected will remain confidential with the study team.

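### Releasing the full system at each participant's own follow-up visit leaves about a month in which earlier completers have access while others still await their retention survey

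*Protocol*

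**What the plan says.** Release of the system is described in two places in the Protocol.

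- Follow-up assessment (under Data collection methods): after the in-person assessment, "returning participants in all arms will be provided with a short code to access the full ARMADILLO system". A proviso postpones this "In the event that the system must undergo substantial revision prior to finalization", in which case participants are to be alerted later by SMS.
- Incentives: "At the end of the full intervention and follow-up period, the full ARMADILLO system will be made available to all study participants".

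The retention interval is protected by two further sentences in the follow-up section: "There will be no contact with participants from any study arm in the eight weeks between the end of the intervention and follow-up", and "The ARMADILLO system will be offline in this period as well".

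The calendar comes from Participants and Timeline. "Recruitment to the trial itself will be rolling over a one month period", and each person is randomized after their baseline survey, "with their seven-week interaction with the appropriate system commencing the following day". The Timeline closes the field phase with "An additional two months until the last-enrolled participant completes their two-month follow-up visit".

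**The concern.** The secondary objective asks whether youth given access keep what they learned longer and more accurately than youth without access. The eight-week interval without contact exists so that this can be measured cleanly. The protocol also gives lower contamination between arms as a reason for running this stage before any wider rollout.

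Release at each person's own visit works against both. Once the first completers have the code, the full content is live in the study communities and in the hands of people from every arm, while later-enrolled participants are still inside their own retention interval. A control participant who has not yet been surveyed could see content through a completer. An intervention participant who is still waiting could be refreshed. Neither exposure would be recorded in a form that the analysis could correct.

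**Working it through.** **Inputs.** Recruitment window about one month (Participants, Timeline), taken as 30 days with a range of 28 to 31. Intervention seven weeks = 49 days (Participants). Follow-up interval eight weeks = 56 days (Follow-up assessment). Dropout up to 20% and site sizes of 720 and 756 (Study sample size). Day 0 is first enrolment. The one-day lag before messages start applies to everyone and cancels.

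**1. The plan's own figure.** The Timeline gives 1 + 2 + 2 = 5 months for the field phase, which reproduces. In days the components are 30 + 49 + 56 = 135, somewhat under five months because the Timeline rounds seven weeks up to two months.

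**2. Length of the overlap.**
- First follow-up and first release: 49 + 56 = day 105.
- Last follow-up: 30 + 49 + 56 = day 135.
- Overlap: 135 − 105 = 30 days.

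The intervention and follow-up lengths cancel, so the overlap equals the recruitment window: 28 to 31 days. Visits are booked at participants' convenience, which can only lengthen it. Simulating 756 participants with an assumed extra delay of 0–7 or 0–14 days gives a spread of about 36 or 42 days.

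**3. How much of the sample is exposed (assuming even enrolment).**
- Mean time between first release and a participant's own survey: 30 / 2 = 15 days. The earliest completers have none; the last enrolled have about four of their eight weeks.
- Surveyed at least 7 days after first release: (30 − 7) / 30 = about 77%.
- Mean share of enrolled participants already holding the code: 0.5 × (1 − 0.20) = 0.40, or 0.40 × 720 = 288 in Peru and 0.40 × 756 = about 302 in Kenya.

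**4. Primary endline.** Last endline: 30 + 49 = day 79. Margin before first release: 105 − 79 = 26 days. The margin equals the follow-up interval minus the recruitment window. With two months counted as up to 61 days it ranges from 56 − 31 = 25 to 61 − 28 = 33 days.

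**5. The offline sentence.** The first participant's no-contact interval runs from day 49 to day 105, while the last enrolled is still using the system from day 30 to day 79. The system must therefore be live between days 49 and 79. Read site-wide, the sentence cannot hold under rolling enrolment; read per participant, it can.

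**6. Effect on power: illustration only.** Take 705 / 3 = 235 per arm and 235 × 0.8 = 188 evaluable. Assume, since the protocol states neither alpha nor SD, a two-sided 5% test with 80% power for a difference of 0.10. The implied SD is 0.10 / [(1.960 + 0.842) × √(2/188)] = 0.346. If 5%, 10%, 20% or 30% of the contrast were lost, power would be about 76%, 71%, 61% or 50%. These losses are assumed, cover dilution only, and borrow a sample size set for the primary outcome.

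**The case against.** The strongest reply is that the documents show an opportunity for contamination and no more. It needs completers to pass the code or the content to people still waiting, and no sharing rate is given. That stands.

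Sharing is also possible without early release. Messages already received stay on the phone, so intervention participants can reread or forward them throughout the eight weeks, and the in-depth interviews ask about sharing. That also stands: release adds the full content, and completers from the control arm, to a route that already exists.

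A reader might infer that the Incentives section contradicts the follow-up section. It does not clearly do so, because its end of follow-up can mean each participant's own. The passages are ambiguous.

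A reader might also infer that half the sample holds the code at a typical visit. Only returning participants receive it, so the figure is nearer 40% at the stated dropout allowance. Nor does staggering by enrolment date confound the arms: blocks of six within age-sex cohorts tend to balance arms over calendar time.

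The safeguards deserve weight but do not close the gap. One youth per household stops sharing between participants in one home, not between neighbours; in Peru all come from one zone of about 50,000 residents. Requiring an own phone does not stop a message being shown or retold. Phone-number tracking cannot see that either, and after release control numbers have legitimate access. Distance between locations in Kenya does not help once completers in every arm hold the code.

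**Conclusion.** The point holds as a risk to the secondary retention comparison. As written, release is participant by participant, and later-enrolled participants await their survey for about 28 to 31 days while earlier completers have live access. The two-week mean overlap and the 40% figure rest on even enrolment, and the latter also on 20% dropout.

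Three stronger readings are not supported. The retention outcome cannot be called contaminated, because exposure depends on unmeasured sharing. The bias cannot be called dilution: exposed controls would shrink the contrast, but refreshed intervention participants could enlarge it. The primary endline is not touched, since on the stated one-month recruitment the last endline precedes the first release by about 25 days or more.

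This is a cheap improvement to an operational rule that the protocol itself fixes. Later analysis could not undo an exposure that nobody recorded.

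**What to change.** - In both Follow-up assessment and Incentives, state that access opens at each site on one date, after that site's last follow-up survey. The overlap from early release then falls to zero.
- At the follow-up visit, tell returning participants that an SMS will announce access. The follow-up section already describes such an alert for the case of system revision; its use would need to be widened.
- Exclude anyone who opted out with STOP, because the unsubscribe message promises no further contact.
- Reword the offline sentence so that it applies to each participant's own eight-week interval.

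The cost is a few sentences and a scheduled SMS. The earliest completers wait until about day 135 instead of day 105, up to about a month longer. The change does not remove sharing of messages already stored on phones.
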